#### Common brain effects of acupoints, pain-related brain regions, and differential brain effects

2.7.4

Analyses of common brain effects elicited by acupoint stimulation will be performed using GingerALE software (Version 3.0.2, http://brainmap.org/ale) with cluster-level family-wise error (FWE) correction. The following parameters will be applied: 5,000 permutations for statistical testing, a cluster-forming threshold of *p* < 0.001, and a statistical significance threshold of *p* < 0.05 (cluster-level FWE corrected) (30). Additionally, a predefined pain-related brain map (derived from the Neurosynth database, https://neurosynth.org) will be used to evaluate spatial overlap between acupoint-induced activation clusters and pain-associated brain regions. The overlap analysis will adopt a statistical significance threshold of *p* < 0.05.

#### Functional decoding

2.7.5

To determine the functional roles of acupoint-induced activation clusters, forward inference and reverse inference analyses will be conducted using the BrainMap database.^1^ Forward inference will decode the behavioral domains (BD) and paradigm classes (PC) associated with the identified brain regions. Behavioral domains are hierarchically categorized into five major classes (*behavioral, cognitive, emotional, interoceptive, and perceptual*) and 51 subclasses. For forward inference, the functional profile of a brain region will be defined by the probability of its involvement in specific behavioral or cognitive tasks based on task-classification labels. Reverse inference will identify the most likely behavioral domains and paradigm classes linked to the functional connectivity patterns of activation clusters using Bayesian probability.^2^ This analysis will quantify the posterior probability that a specific brain region is engaged during a particular task or behavioral context.

The significance of forward and reverse inference results will be assessed using likelihood ratio tests and chi-square tests, respectively. A false discovery rate (FDR) correction for multiple comparisons will be applied to both analyses, with a significance threshold of *p* < 0.05.

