#### Statistical analysis

2.7.3

Neuroimaging analyses will be conducted using the SPM12 toolbox on the MATLAB platform. First, one-sample *t*-tests will be performed to identify brain activation patterns associated with verum acupuncture (at true acupoints) and sham acupuncture (at non-acupoints). Subsequently, repeated-measures analysis of variance (ANOVA) will be applied. If statistically significant effects are detected, paired-sample t-tests will be conducted between the two groups to identify differential brain activation patterns between true acupoints and non-acupoints. Additionally, paired-sample *t*-tests will be performed to compare: (1) Resting-state functional activity pre- versus post-acupuncture; (2) Resting-state activity (pre-acupuncture) versus task-based activity (during acupuncture). A voxel-wise threshold of *p* < 0.005 with a false discovery rate-corrected cluster level of *p* < 0.05 was applied in the task fMRI analysis. Significant activation clusters will be visualized and localized using the xjView, MRIcron, and BrainNet Viewer toolboxes within the MATLAB platform.

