#### Common brain effects

3.1.1

Both verum and sham acupuncture may commonly activate a brain network involving the anterior cingulate cortex, anterior insula, primary/secondary somatosensory cortices, and prefrontal cortex. This network is responsible for processing stimulus salience, bodily sensations, and cognitive appraisal, reflecting the non-specific effects of acupuncture. That is, this brain activity largely stems from shared components such as attention, sensation, and expectation elicited by the skin penetration itself, overlapping with the neural substrates of placebo effects.

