### Functional decoding analysis

3.4

Decoding via databases like BrainMap will reveal that the brain clusters activated by verum acupuncture are associated with functional domains far beyond mere “sensory processing.” major behavioral domains (BD) and paradigm classes (PC) include areas such as sensation, perception, and interoception.

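### Functional decoding and pain-map overlap are specified only for acupoint clusters, with no sham or verum-sham counterpart, so their results cannot be separated from non-specific effects

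*Protocol article*

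**What the plan says.** Section 2.7.5 names one input to the BrainMap analysis: "To determine the functional roles of acupoint-induced activation clusters, forward inference and reverse inference analyses will be conducted using the BrainMap database". Section 2.7.4 uses the same input for the Neurosynth map, which will serve to "evaluate spatial overlap between acupoint-induced activation clusters and pain-associated brain regions". The term acupoint-induced is not defined. Section 2.7.3, however, uses acupoint and non-acupoint to mean verum and sham, when it plans one-sample tests for "brain activation patterns associated with verum acupuncture (at true acupoints) and sham acupuncture (at non-acupoints". The expected result in section 3.4 points the same way: it says that "the brain clusters activated by verum acupuncture are associated with functional domains far beyond mere" sensory processing, and that the leading domains "include areas such as sensation, perception, and interoception".

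Section 2.7.3 also plans a paired test of true acupoints against non-acupoints, to follow if the repeated-measures ANOVA is significant. No sentence takes the sham map or this contrast into the overlap or the decoding. The heading of 2.7.4 mentions differential effects, but its text describes no differential analysis.

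Section 3.1.1 states the expectation for the shared response: "Both verum and sham acupuncture may commonly activate a brain network involving the anterior cingulate cortex, anterior insula, primary/secondary somatosensory cortices, and prefrontal cortex". It adds: "This network is responsible for processing stimulus salience, bodily sensations, and cognitive appraisal, reflecting the non-specific effects of acupuncture". The first objective in the Introduction is to separate the specific central effects of an acupoint from non-specific responses by means of the sham control.

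**The concern.** Decoding and overlap take a set of clusters and ask what those brain locations are known for. If the clusters come from needling at the acupoint alone, they include whatever attention, touch and expectation contribute, and by the protocol's own account these arise under the sham needle too. The planned tests ask whether clusters map to a behavioural domain or coincide with a pain map. None of them asks whether verum differs from sham.

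This matters because the Discussion presents forward and reverse inference as the step from describing locations to interpreting mechanism, and section 3.5 says that the design can dissociate placebo components from specific ones. These two interpretive analyses leave out the control that such a separation needs. A reader of the eventual report could take the behavioural labels or the pain overlap as properties of acupuncture when the sham needle would have earned the same ones.

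**Working it through.** The protocol gives no figure for this point, so there is none to reproduce. The check is mainly a comparison of sections.

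**1. Which maps are produced and which are used**

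| Map (section 2.7.3) | Pain overlap (2.7.4) | Decoding (2.7.5) |
|---|---|---|
| Verum, one-sample | yes, reading acupoint-induced as in 3.4 | yes, same reading |
| Sham, one-sample | not stated | not stated |
| Verum against sham, paired, if the ANOVA is significant | not stated | not stated |

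**2. Expected labels against the shared network**

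- Section 3.1.1 gives the network common to verum and sham three functions: salience, bodily sensation and cognitive appraisal.
- Section 3.4 expects the verum decoding to return sensation, perception and interoception.
- The two lists are close. The expected decoding result is thus one that the shared network could produce on its own.

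**3. The case of no difference**

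The labels depend only on where the clusters lie. If the verum and sham maps were identical, the planned decoding and overlap would give the same results for verum as they would for sham. Significant labels would still be reported, because the likelihood-ratio, chi-square and overlap tests involve no sham term.

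**4. Illustration of what each map retains**

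Inputs from the protocol: n = 30 per acupoint (section 2.3) and voxel p < 0.005 (section 2.7.3). Assumptions: a one-sided one-sample t-test, a standardised effect d equal under verum and sham, and no cluster correction.

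P(voxel enters the verum map) = P(T > t₀.₉₉₅,₂₉), where T is noncentral t with 29 degrees of freedom and noncentrality d√30.

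| Assumed d | P(enters verum map) | P(enters verum-minus-sham map), true difference 0 |
|---|---|---|
| 0.5 | 0.503 | 0.005 |
| 0.8 | 0.939 | 0.005 |
| 1.0 | 0.995 | 0.005 |

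The verum map keeps the shared response, and the difference map removes nearly all of it.

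**5. How much of the verum map is shared**

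Let s be the assumed fraction of responding voxels that are shared, p_c the detection probability for shared voxels and p_s that for verum-only voxels. The shared fraction of the map is s·p_c / [s·p_c + (1 − s)·p_s]. With shared d = 0.8 (p_c = 0.939) and verum-only d = 0.5 (p_s = 0.503):

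- s = 0.3: 0.445
- s = 0.5: 0.939 / (0.939 + 0.503) = 0.651
- s = 0.7: 0.813
- s = 0.9: 0.944

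With equal d for both kinds of voxel, the shared fraction of the map is simply s. The result follows the assumed s, so the protocol does not determine whether the shared part is a minority or a majority.

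**The case against.** **The input is not formally defined.** Acupoint-induced is tied to no particular contrast, and a verum-minus-sham reading is conceivable. The clearest link to verum is in a paragraph of anticipated results, not in the methods. This stands as a reason for caution. Still, the acupoint/non-acupoint wording of 2.7.3 and the expectation in 3.4 both favour the verum reading. If another was meant, one sentence would settle it.

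**An article may leave this to a fuller document.** Silence about sham decoding does not prove that none will be done. But the article is not silent on these analyses: it names the input, the tests, the multiplicity correction and the expected conclusion. The input it fixes does not serve its stated objective.

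**Decoding is description, and specificity is tested elsewhere.** Much of this stands. Verum decoding validly describes which functions are linked to regions active during needling, and the paired test in 2.7.3 addresses differences in activation. That test does not protect the decoding, though, because the labels are obtained without reference to it.

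**Verum is expected to do more.** A reader might infer that the labels will come mostly from the non-specific network. The documents do not support that. Section 3.1.2 also expects hypothalamic, brainstem, amygdala and hippocampal responses to verum, which would be decoded too, and section 3.1.1 says only that the shared activation may occur.

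**Conclusion.** The point holds in this form: as specified, decoding and pain overlap describe the response to needling at the acupoint without a sham reference, so their results cannot be separated from the components the protocol calls non-specific. They would be the same if verum and sham maps were identical, and they do not serve the objective of isolating specific effects.

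The conclusion rests on reading acupoint-induced as verum, which the text favours without defining, and on the protocol's own expectation of a shared network. The detection probabilities in the working depend on assumed effect sizes and ignore cluster correction; they show the direction of the problem, not a forecast.

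Two stronger readings go too far. One is that the labels will be predominantly non-specific: that share is unknown. The other is that verum decoding can say nothing about acupuncture: it can describe, but it cannot show specificity against sham. The primary outcomes, brain activity and connectivity, are not affected by this point. The change should be made before the decoding is used for mechanistic interpretation.

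**What to change.** In sections 2.7.4 and 2.7.5:

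- State which map or contrast supplies the acupoint-induced clusters.
- State that the same overlap and the same forward and reverse inference will be run on the sham map and, where the paired test in 2.7.3 yields clusters, on the verum > sham and sham > verum clusters.
- Report the verum decoding as descriptive, side by side with sham.
- Base any statement of verum-specific function or pain overlap on the verum-sham contrast or on a direct comparison of the verum and sham profiles.
- Note that the contrast reflects needle penetration and site together, since the sham in section 2.5.2 differs in both. A difference therefore does not by itself establish acupoint specificity.

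Reword section 3.4 to match.

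The cost is a few more runs of software already planned on maps already planned, plus edits to three sections. No new data are needed. The downside is that the contrast may give few clusters to decode, or none, particularly as the paired test depends on a significant ANOVA. In that case the side-by-side report remains, and no verum-specific label should be claimed unless the direct comparison of profiles supports it.

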#### Statistical analysis of baseline information and C-MMASS

2.7.6

Statistical analyses of participants’ baseline characteristics and inter-group comparisons of C-MMASS scores will be performed using SPSS software (version 26.0). Categorical variables between groups will be analyzed with the chi-square test, while continuous variables will be assessed using independent samples *t*-tests. Within-group comparisons of categorical variables (pre- vs. post-intervention) will employ the chi-square test, and continuous variables will be evaluated with paired samples *t*-tests. All quantitative data will be presented as mean ± standard deviation. A threshold of *p* > 0.05 will indicate no statistically significant difference.

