### Study design

2.1

This prospective, single-center, randomized, single-blind, placebo-controlled study will enroll 250 healthy participants. Participants will undergo acupuncture in separate sessions at one of seven predefined acupoints (verum acupuncture) and its corresponding non-acupoint (sham acupuncture), with a 1-week interval between sessions (18) (Figure 1). All participants will undergo two identical fMRI scanning sessions, separated by a 1-week interval, which corresponds to the washout period between the two acupuncture interventions. Each session will include resting-state fMRI scans before and after acupuncture, as well as task-based fMRI scans during acupuncture (Figure 2). The sequence of verum and sham protocols will be randomized across all fMRI runs, and the order of presentation will be counterbalanced across subjects (18).

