### Sample size

2.3

Currently, there are no standardized criteria for determining sample sizes in MRI studies, as they are often constrained by practical considerations such as scanning time and cost. Based on an efficiency analysis of sample size estimation in MRI research, a previous study indicated that approximately 12 participants are required to achieve 80% power at the single-voxel level for typical activation effects (19). In line with this reference and considering the study design, we set a sample size of 30 participants per acupuncture point. Each volunteer will undergo both verum and sham acupuncture at the same acupoint, resulting in a total of 210 experimental sessions. To account for potential data loss due to head motion or participant dropout, we plan to enroll a total of 250 subjects.

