### Randomization, allocation concealment, and blinding

2.4

In this study, participants will be randomly assigned to one of the seven acupoint groups. The randomization sequence is generated using SPSS 26.0 software, and the allocation scheme is concealed using opaque sealed envelopes. Upon participant enrollment, the allocation will be revealed by sequentially opening the envelopes to determine the assigned acupoint for acupuncture. The blinding procedure involves three aspects: first, participants are blinded to the specific acupoints used in the trial; they are only informed that the acupoints are located in the distal limbs. Second, radiologists, due to their professional constraints, are unaware of the specific acupoints and their significance, ensuring the objectivity of the scanning process. Third, image processors are blinded to the participants’ group assignments, ensuring the objectivity of the image processing.

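### Section 2.7.6 assigns an independent-samples t-test to the between-group C-MMASS comparison, although verum and sham scores come from the same participants

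*Protocol article*

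**What the plan says.** The design is within-person for needling condition. Section 2.3 states: "Each volunteer will undergo both verum and sham acupuncture at the same acupoint". Section 2.1 adds: "All participants will undergo two identical fMRI scanning sessions, separated by a 1-week interval", and says of the two conditions that "the order of presentation will be counterbalanced across subjects". The only between-person factor is the acupoint: "participants will be randomly assigned to one of the seven acupoint groups" (section 2.4). The planned size is 30 participants per acupoint, with 250 enrolled (section 2.3). Section 2.6.4 has participants rate Deqi on the C-MMASS once both trials are complete, each sensation from 0 to 10.

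Section 2.7.6 covers baseline characteristics and between-group comparisons of C-MMASS scores. For comparisons between groups it names the chi-square test for categorical variables, and then: "while continuous variables will be assessed using independent samples" t-tests. Paired t-tests appear there only for within-group comparisons before and after the intervention. The categorical counterpart reads: "Within-group comparisons of categorical variables (pre- vs. post-intervention) will employ the chi-square test".

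The section does not define its groups. Elsewhere the article uses the word for both factors: sections 2.5.1 and 2.5.2 are headed as the verum and sham groups, section 2.7.3 compares true acupoints with non-acupoints as two groups by paired t-tests, and section 2.4 speaks of seven acupoint groups.

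**The concern.** On the natural reading, the C-MMASS comparison is verum against sham. Both scores come from the same person, and the named test treats them as coming from different people. Sections 2.7.3 and 2.7.6 then handle the same contrast in opposite ways, one as paired and the other as independent.

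According to the Abstract, the C-MMASS and the blinding assessment are collected to judge the credibility of the sham and the Deqi sensation. A test that ignores positive pairing has too large a standard error and can miss a real difference in sensation. Section 2.7.6 labels any p-value above 0.05 as no statistically significant difference, so a miss could be reported as similar sensation under verum and sham.

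**Working it through.** **Plan's own figure.** None exists for this comparison. The article gives no C-MMASS effect size, SD, power or within-person correlation. The only related arithmetic is 7 × 30 = 210 participants, and 210 / 250 = 0.84, so enrolment allows for 16% loss.

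**Inputs.** From the article: 30 pairs per acupoint (section 2.3), 210 pairs if all acupoints are pooled, and the 0.05 threshold (section 2.7.6). Assumed: a two-sided test, equal SDs s, normal scores, within-person correlation ρ of 0.3, 0.5 or 0.7, and differences d of 0.2 to 1.0 SD.

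**Step 1, standard error.** For n pairs:

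- SE used by the independent test: s√(2/n)
- True SE of the verum-sham difference: s√(2(1−ρ)/n)
- Ratio: 1/√(1−ρ) = 1/√0.7 = 1.20, 1/√0.5 = 1.41, 1/√0.3 = 1.83

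**Step 2, true type I error at nominal 5%.** The large-sample value is 2Φ(−1.96/√(1−ρ)), which gives 1.9%, 0.6% and 0.03%. Simulation (20,000 runs) gives about 2.0%, 0.6% and 0.1% with 30 pairs, and 1.9%, 0.5% and 0.04% with 210. The paired t-test stays between 4.8% and 5.3%. At ρ = 0 the independent test is correct. At ρ = −0.3 its type I error is about 8.4% with 30 pairs.

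**Step 3, power (simulated), independent / paired.**

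| Pairs | Assumed d | ρ = 0.3 | ρ = 0.5 | ρ = 0.7 |
|---|---|---|---|---|
| 30 | 0.5 SD | 47% / 61% | 47% / 75% | 47% / 93% |
| 30 | 0.8 SD | 90% / 95% | 93% / 99% | 97% / 100% |
| 30 | 1.0 SD | about 99% or more / 99.5% or more | same | same |
| 210 | 0.2 SD | 54% / 69% | 55% / 82% | 56% / 96% |
| 210 | 0.5 SD | about 100% / about 100% | same | same |

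The near-constant 47% is particular to d = 0.5 with n = 30. The expected t is 0.5/√(2/30) = 1.94, almost on the critical value of 2.00, so rejection stays near one half whatever ρ is. At d = 0.3, n = 30 and ρ = 0.5 the powers are about 13% and 35%.

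**Step 4, the other reading.** If the groups are the seven acupoints, the people differ and independence holds, but a t-test compares two groups only. Covering seven would take 7 × 6 / 2 = 21 pairwise tests. Unadjusted, and treated as independent for illustration, their familywise error is 1 − 0.95²¹ = 66%. Chi-square is valid for categorical variables on this reading.

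**Step 5, paired categories.** For paired binary data with an assumed proportion of 0.5 and 30 pairs, simulation (5,000 runs) puts the chi-square type I error at 1.9% for ρ = 0.3 and 0.5% for ρ = 0.5. McNemar's test gives 4.1% and 4.4%.

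**The case against.** The case for leaving this alone is that little depends on it. The primary outcomes are fMRI measures, and section 2.7.3 pairs the verum-sham imaging contrast correctly. At positive correlation the error is conservative and does not inflate false positives. Verum penetrates the skin and is manipulated after Deqi, while sham is blunt and does not penetrate, so a large difference in sensation is plausible (an inference, not a stated figure). In that case either test would find it. Nor does section 2.7.6 say that C-MMASS is tested only within groups of 30. All of this stands and limits the consequences. It does not make the named test right, and small differences, single sensations or contrasts within one acupoint remain exposed.

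A reader might infer more than the article supports:

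- That group comparisons generally are wrong. The imaging contrasts are paired, and chi-square across the seven acupoint groups is valid.
- That C-MMASS is to be tested before against after, or that baseline data are to be compared between verum and sham. Section 2.7.6 assigns C-MMASS only between-group comparisons, and nowhere states that baseline is compared by condition.
- That the chi-square test for pre/post categories will distort a particular result. The test is unsuitable for paired data, but no pre/post categorical variable is listed: demographics are collected at baseline, and treatment guesses after both sessions.
- That the article will conclude equal Deqi from a non-significant result. Its explicit reasoning from non-significance, in section 3.5, concerns the guesses.

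**Conclusion.** The independent-samples t-test is the wrong test for C-MMASS on either reading of the word groups. For verum versus sham it contradicts both the within-person design and section 2.7.3; for seven acupoints it does not fit the number of groups.

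The size of the effect depends on assumptions, since the article gives neither a correlation nor an expected difference. At correlations of 0.3 to 0.7 the standard error is 20% to 83% too large. With 30 pairs and a 0.5 SD difference, the loss of power is roughly 14 to 46 percentage points. It becomes small at about 1 SD with 30 pairs, and negligible at 0.5 SD with 210 pooled pairs, though not at 0.2 SD even when pooled. The direction is conservative unless the correlation is negative.

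Because C-MMASS is not a primary outcome and the raw data are unaffected, this should be fixed but does not threaten the main conclusions.

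**What to change.** Revise section 2.7.6 before analysis:

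- State whether groups means verum and sham or the seven acupoints, separately for each comparison.
- Compare verum and sham C-MMASS scores with a paired t-test or Wilcoxon signed-rank test. Alternatively, use a mixed model with participant as random effect and condition, session, acupoint and condition × acupoint as fixed effects. The model uses all acupoints together and allows for session order.
- Across the seven acupoint groups, use ANOVA or Kruskal-Wallis for continuous variables and keep chi-square for categorical ones.
- For any paired categorical comparison, replace chi-square with McNemar's test (two categories) or the Stuart-Maxwell test (more than two).

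The cost is a few sentences. No new data, participants or scanning are needed. Making the change now avoids choosing the test after the scores have been seen.
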